### Recruitment strategies

A combination of the following strategies will be employed for recruiting T1DM patients: (i) invitation letters will be sent to T1DM patients included in the T1DM cohort that has been established by our research team, (ii) flyers and posters will be posted within the hospital, and (iii) online advertisements will be published on WeChat—a social network platform—public accounts, and doctors and diabetologists will be asked to spread the information. WeChat has been chosen for its broad use among smartphone users in China [18]. Any interested respondents will be provided with the details about the trial and will be assessed for their eligibility by a diabetologist according to the eligibility criteria listed in Table 2 through a face-to-face consultation.

### Intervention assignments

#### Randomization and sequence generation

All participants who meet the inclusion criteria for participation and who sign the informed consent form will be randomized by an independent research member. Blocked randomization will be adopted to assign patients to the two groups at a 1:1 ratio with random block sizes [19]. The random sequence will be generated with SPSS 25 by a statistician [20].

#### Allocation concealment

Allocation concealment will be achieved through sequentially numbered, opaque sealed envelopes. The random sequence will be generated by a statistician who will not be involved in the patient enrollment and baseline assessment process. The envelope will only be opened for each patient after consent is obtained, eligibility is confirmed, and the baseline evaluation is finished.

#### Blinding

Due to the nature of the smartphone app used in this RCT, it is impossible to blind patients and clinicians. However, blinding of outcome assessors and data analysts will be ensured. Data entry will be accomplished by individuals external to the research team, and data analysis will be completed without referring to the allocation information. Patients and clinicians will be strongly discouraged from disclosing group assignment information to the outcome assessors. To overcome the lack of participant and clinician blinding, the objective outcome HbA1c has been chosen as the primary outcome. It is well recognized that a lack of blinding has a minimal impact on the assessment of objective outcomes [21].

### Intervention

The study interventions will last for 24 weeks. Patients in each of the two groups will be encouraged to continue their previous insulin treatment regimen, with either multiple daily injections or insulin pumps. All the interventions will run concurrently. Patients allocated to the smartphone app group—the automated, individualized education group—will attend a course on the use of the app provided by the research team. The course will be given to the two groups of patients separately to reduce possible contamination.

#### Automated and individualized education through an app and artificial intelligence

Patients allocated to the individualized group will be given instructions to install the app, which includes the following modules: glycemic management, diabetes knowledge assessment, diabetes-related scientific knowledge promotion, patients’ service, materials for a diabetes SEP, and messages (Fig. 2).

**Fig. 2 Fig2:**
[figure not shown]
Homepage of the smartphone app (Yi Tang Yun Qiao). **a** The English translation and explanation of homepage. **b**–**d** The diabetes knowledge assessment module. **e** Different aspects and levels of SEP diabetes education materials. Keys: SEP, structured education program

**Fig. 3 Fig3:**
[figure not shown]
Full Standard Protocol Items: Recommendations for Interventional Trials (SPIRIT) figure

Through the glycemic management module, patients can keep diaries on blood glucose, diet, exercise, medication, height, and weight. To reduce the data entry burden, the results on blood glucose could be transferred from glucose meters to the app through Bluetooth or General Packet Radio Service. Daily step count data could be obtained from the step counter software in the smartphone, and diet information could be recorded by taking photos of the food through the built-in camera [13].

The diabetes knowledge assessment module (Fig. 2b–d) includes self-administered questionnaires that were designed to assess patients’ diabetes-related knowledge. The module serves to assess patients’ baseline diabetes-related knowledge. A popped-up box will be used as a reminder each time patients begin browsing the diabetes SEP in the automated, individualized education group.

The diabetes-related scientific knowledge promotion module provides general knowledge on T1DM, including an overview of T1DM, complications related to T1DM, insulin treatment, etc.

The patient’s service module provides access to electronic medical records including (i) the laboratory results (e.g., HbA1c test results) and (ii) diagnosis and treatment records (e.g., diabetes-related complications and their corresponding treatments). This module will keep both patients and clinicians well informed about a particular patient’s diabetes care. Online outpatient registration and off-line appointments with clinicians are also available for patients.

The diabetes SEP material (Fig. 2e) includes two parts. Part 1 serves the individualized education purpose, which has a push notification function that provides recommended education materials that meet the needs of the patient by considering his/her baseline diabetes-related knowledge. Part 2 provides a database that includes digital SEP material developed by our research team. Patients can browse or choose any content according to their interests. No push notification is included in part 2.

The message module facilitates patient-doctor communication through various means: typing words, sending pictures or short videos, sending voice messages, and live chatting. The patient and his/her doctor will establish a blood sugar target collaboratively. The doctor will review the patients’ diabetes diary once a week and provide feedback to patients: (i) give positive feedback if patients are keeping the target well, (ii) alert patients if they are off-target, and (iii) provide other tailored feedback by considering patients’ conditions. Furthermore, whenever a patient’s blood glucose level is dangerous (< 3.9 mmol/L or > 20.0 mmol/L), an alert will be automatically sent to the doctor, and an immediate phone call will be made to the patient by the doctor [13].

#### Routine care

Patients allocated to the routine care group will receive the education provided by health-care professionals in the outpatient department. They will not be asked to use any smartphone app during the trial. This trial will not require alteration in the use of any medication to both trial arms.

### Approaches to improve adherence to the intervention

Two strategies will be utilized to encourage the participants’ usage of and adherence to the recommendations of the app. First, adherence reminders will be provided by our health care professionals during every face-to-face visit at the outpatient department and telephone interviews every 4 weeks. Second, we will award the top three most frequent users every month with small gifts.

### Outcomes

Both subjective and objective outcomes will be included in the outcome measurements. Due to the nature of the study design, it is impossible to blind the patients and personnel in the trial. Therefore, we will choose HbA1c, a laboratory-tested index, to reduce potential bias induced by the lack of blinding of participants and personnel. We will also include patient-reported outcomes (e.g., quality of life) to provide a comprehensive assessment of the treatment effect. Detailed explanations of the outcome measurements are provided below.

#### Primary outcome

HbA1c has been chosen as the primary outcome for its ability to reflect patients’ average level of blood glucose over the past 2 to 3 months. It is the gold standard for evaluating the long-term effect of glycemic management and has been proven to be associated with the risk of developing various complications [22]. Peripheral blood will be collected during the hospital visit at the request of the patients’ doctor during each scheduled follow-up time point (baseline, week 12, and week 24). The HbA1c test will be performed by the Central Laboratory, which has been certificated by the International Federation of Clinical Chemistry and Laboratory Medicine (IFCC).

#### Secondary outcomes

Due to the complex nature of T1DM, it is important to include a wide spectrum of outcomes to measure the treatment effect. Therefore, physiological parameters, psychosocial outcomes, and psychological outcomes are included in the secondary outcomes.

Time in range (TIR) of 70–180 mg/dL (3.9–10 mmol/L) will be used as a secondary outcome to overcome the inability of HbA1c to provide information on patients’ hypoglycemia, glycemic variability, or daily patterns of glycemia [23]. TIR is a newly recognized indicator of glycemic management by both clinicians [23] and patients [24]. TIR data will be collected using a continuous glucose monitoring system (iPro2, Medtronic). Data on other physiological parameters including fasting blood glucose (FBG), levels of cholesterol and triglycerides, blood pressure, and body mass index (BMI) will be also collected as the secondary outcome (Table 1).

The valid and reliable diabetes quality of life (DQOL) scale [25] is a widely used 46-item tool for assessing the quality of life related to diabetes in terms of three aspects: diabetes satisfaction (15 items), impact (20 items), and worry (11 items). Each item is answered on a 5-point Likert scale, with a score of 1 representing “always affected,” “always worried,” or “never satisfied” and a score of 5 indicating “no impact,” “no worries,” or “always satisfied”. A higher total score reflects a better quality of life. A Chinese version of the DQOL scale has been translated [26] and validated [27] in the diabetic population from mainland China and will be adopted in this trial.

Diabetes self-care behaviors will be assessed with the Summary of Diabetes Self-Care Activities (SDSCA) measure, which contains six behavior-related scales: general diet, specific diet, glucose monitoring, physical activity, foot care, and smoking. Absolute weekly frequency or consistency of diabetes self-care activities are scored with a scale ranging from 0 to 7, with higher scores reflecting better performance in self-care behaviors. The internal consistency reliability and construct validity of the SDSCA was supported by its psychometric test based on an adult diabetes population [28]. A validated Chinese version of the SDSCA is available for this trial [29].

Patients’ diabetes-related psychosocial self-efficacy will be evaluated with the Diabetes Empowerment Scale-Short Form (DES-SF), which is a short form of the Diabetes Empowerment Scale developed based on the American population with type 1 or type 2 diabetes [30, 31]. A revised Chinese version is available for the mainland China population [32]. The Chinese version of the DES-SF includes 8 domains with 1 item for each, covering the need for change, making a plan, overcoming barriers, seeking support, maintaining optimism, supporting oneself, diabetes-related pressure relief, and making the appropriate choice according to individual conditions for self-diabetes care. Each item is answered on a 5-point Likert scale, with 1 indicating strongly disagree and 5 indicating strongly agree. The total score ranges from 8 to 40, with a higher total score reflecting better psychosocial self-efficacy.

Patient psychological status, including depression and anxiety, will be assessed with the Beck’s Depression Inventory (BDI) and the State-Trait Anxiety Inventory (STAI) respectively. The Chinese version of the BDI consists of 21 self-rated items [33]. Each item will be scored from 0 to 3, with a total score ranging from 0 to 63, and a higher score indicates more serious depression. The Chinese version of the STAI consists of two subscales to measure both state and trait anxiety states [34]. Each of the two anxiety states will be measured with a 20-item subscale, and each item will be scored from 1 to 4. The total score for both state and trait anxiety ranged from 20 to 80, with higher scores indicating more serious anxiety. Data on patients’ satisfaction will also be collected through verbal rating grading, which involves ordering a four series of adjectives from lightest to strongest satisfaction.

Patients’ engagement with the app will be measured in terms of communications with the clinician and the utilization of the smartphone app. Specifically, the number of messages with education materials sent to the patients, the number of and delay of in message responses, the number of video calls/phone calls with patients, the number of logs entered entries by patients, and the time spent in the diabetes SEP diabetes education module will be collected.

Safety-related outcomes, including hypoglycemic events, hospitalization, and emergency room visits, will be collected at each follow-up time point.

### Data management and statistical analysis

#### Data collection

Primary and secondary outcomes will be collected by qualified research members at three face-to-face follow-up time points: baseline, week 12, and week 24. Data input will be double-checked by two independent research members. Patients’ compliance data and the number of communications with patients through the app will be collected and stored in the backend database of the app. Safety-related outcomes will be collected at each follow-up time point, including telephone interviews.

#### Data management

All the hardcopies of the patient report forms (PRFs) will be retained in locked cabinets in numerical order. Access to the PRFs and trial data will be restricted. All collected data will be transformed into electronic forms weekly. All data will be entered electronically by individuals not involved in the trial within 1 week after the data collection. The entered data will be kept in a separate secure location as an electronic backup. Double data entry will be adopted to reduce manual mistakes. Two versions of the entered data will be compared, with disagreements resolved by referring to the original hardcopy PRF. A random subset of data will be selected for quality control purposes after the completion of data entry. Data from selected PRFs will be compared against the entered data. Further mechanisms will be used for data integrity, including referential data rules, range checks, valid value checks, and consistency checks. All amendments of data entered in the database will be documented as well. Interim auditing of the RCT will be conducted upon recruiting half of the proposed number of patients.

#### Data analysis

The primary data analysis will be conducted by using data collected at week 24 under the intention-to-treat principle by including all the randomized patients in the data analysis. Missing data will be filled in with a multiple imputation method under the “missing at random” assumption [35]. Any substantial difference in baseline characteristics will be adjusted with mixed-model regression analysis. Between-group differences will be assessed for the smartphone app group versus the routine care group. Relative risk reductions with 95% CIs will be calculated for dichotomous outcomes. The mean difference with standard deviation (SD) will be used to measure the treatment effect for continuous outcomes.

Secondary data analysis will use data collected at week 12 and week 24. All analyses will follow the same template as the primary data analysis by using a mixed model to adjust for imbalanced baseline characteristics. Linear regression will be used for continuous outcomes, and logistic regression will be used for binary outcomes. Model assumptions will be checked by regression diagnostics for all regression models. Predefined moderators including psychological and psychosocial mediators (e.g., depression, anxiety, self-efficacy) will be examined for treatment interactions. The Bonferroni method will be adopted to adjust the significance level under the circumstance of multiple testing. Furthermore, longitudinal analysis in which data collected at baseline, week 12, and week 24 will be jointly analyzed with appropriate mixed models. The time point will be included as a categorical fixed factor with the first-order autocorrelation of the errors and random intercepts. Monthly data collected on HbA1c during the intervention period will be analyzed with similar mixed models.

A sensitivity analysis will be conducted by using per-protocol data and excluding those patients who drop out of the RCT. The results from the sensitivity analysis might provide some pragmatic evidence from the real world regarding the effectiveness of the smartphone app for controlling T1DM. All statistical tests will be two-sided, with *p* < 0.05 considered to indicate statistical significance.

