## Methods

### Overview of the study design

This single-blinded, 24-week, parallel-group randomized controlled trial with a 1:1 allocation ratio will be conducted in Changsha, China. Patients with T1DM will be randomly allocated into one of two groups: automated, individualized education through an app, and artificial intelligence or routine care. The intervention will last for 24 weeks. The primary outcome will be the change in HbA1c from baseline to week 24 (see flowchart in Fig. 1).

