### Sample size estimation

We propose to enroll 138 T1DM patients including withdrawals, 69 in the smartphone app group and 69 in the routine care group. The sample size estimation is based on the hypothesized changes in the primary outcome HbA1c. Details are presented below.

The primary analysis will compare the level of HbA1c between the smartphone app group and the routine care group. In a recent meta-analysis [11], data from seven RCTs that compared the difference in HbA1c between smartphone app and usual care groups were extracted, and the pooled mean difference was − 0.6%, which was used as the expected effect of this RCT. Using a two-sided hypothesis test at a 5% significance level, with an allocation ratio of 1:1, a total of 110 T1DM patients will be needed to detect a difference in HbA1c between the smartphone app group and routine care group of 0.6% with 80% power. The withdrawal rate among the RCTs included in the meta-analysis ranged from 0.0 to 26.4%, with a median of 8.4% [11]. We conservatively used a drop-out rate of 20%, yielding a total sample size of 138 (69 in the smartphone app group and 69 in the routine care group).

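### Baseline adjustment of the primary HbA1c comparison is conditional on observed imbalance, and the primary outcome is defined as change in some places and level in others; prespecified ANCOVA would settle both

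*Protocol article*

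**What the plan says.** All references are to the protocol article.

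- **Adjustment rule (Data analysis).** "Any substantial difference in baseline characteristics will be adjusted with mixed-model regression analysis". No covariate is named and no criterion for a substantial difference is given. The next paragraph describes the secondary analyses as following the template of the primary one, "using a mixed model to adjust for imbalanced baseline characteristics. Linear regression will be used for continuous outcomes".
- **Data used (Data analysis).** "The primary data analysis will be conducted by using data collected at week 24", by intention to treat with multiple imputation. A joint model of baseline, week 12 and week 24 appears separately, among the secondary analyses.
- **Outcome as change (Overview of the study design; likewise the Abstract).** "The primary outcome will be the change in HbA1c from baseline to week 24".
- **Outcome as level (Sample size estimation).** "The primary analysis will compare the level of HbA1c between the smartphone app group and the routine care group". The Data set table also lists the HbA1c level at 24 weeks as the primary outcome.
- **Baseline HbA1c.** It is scheduled for every patient (Table 1), and the baseline evaluation is finished before the allocation envelope is opened (Allocation concealment).

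**The concern.** The covariate set of the primary test depends on what the data show after randomisation. Under proper randomisation any imbalance is due to chance, so observed imbalance is a poor reason to adjust. The good reason is that a covariate predicts the outcome, and baseline HbA1c would be expected to do so in every trial, balanced or not. Adjusting only when imbalance appears discards most of the precision that the measurement offers.

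The endpoint wording compounds this. With baseline HbA1c always in the model, change and level give the same treatment estimate, so the mismatch would be harmless. Without it, they are two tests with different variances that can reach opposite conclusions on the same data. What is at stake is precision, and a primary test that the article does not pin down.

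**Working it through.** **Inputs from the article.** Two-sided 5% test, 1:1 ("Using a two-sided hypothesis test at a 5% significance level, with an allocation ratio of 1:1"); difference of 0.6 percentage points at 80% power ("routine care group of 0.6% with 80% power"); 110 evaluable, so 55 per arm; 20% drop-out; 138 enrolled.

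**Inputs the article does not give (assumptions).** The SD of HbA1c; the correlation r between baseline and week 24 (range used: 0.3 to 0.7); the trigger for a substantial difference (p<0.05 on baseline HbA1c, with p<0.20 as an alternative).

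**Step 1: the plan's own figures.** 110/(1 − 0.20) = 137.5, rounded up to 138, which reproduces. The 110 cannot be reproduced without an SD. Back-solving: SD = 0.6 × √(55/2) / (1.960 + 0.842) = 0.6 × 5.244 / 2.802 = 1.12 by the normal approximation. With the t-test, SD 1.11 gives N=110 and power 80.2%.

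**Step 2: variances.** Take equal SDs at both visits and set the variance of the unadjusted level comparison to 1. The change score then has variance 2(1 − r), ANCOVA has 1 − r², and the ratio of ANCOVA to change is (1 + r)/2.

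| r | Level | Change | ANCOVA | ANCOVA ÷ change |
|---|---|---|---|---|
| 0.3 | 1 | 1.40 | 0.91 | 0.65 |
| 0.5 | 1 | 1.00 | 0.75 | 0.75 |
| 0.7 | 1 | 0.60 | 0.51 | 0.85 |

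ANCOVA has the smallest variance in every row. In evaluable patients for 80% power (SD 1.12, normal approximation), level needs 110 throughout, change needs 154, 110 and 66, and ANCOVA needs 100, 84 and 56.

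**Step 3: what the conditional rule recovers.** I simulated trials with 55 per arm, SD 1.11 and a true difference of 0.6, adjusting for baseline HbA1c only if its between-group p-value was below 0.05. One-point ranges reflect simulation error.

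| r | Conditional, level | Conditional, change | ANCOVA always |
|---|---|---|---|
| 0.3 | 81% | 67% | 83-84% |
| 0.5 | 81% | 81% | 90% |
| 0.7 | 82% | 95-96% | 97-98% |

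The reason is simple: under randomisation a p<0.05 trigger fires in 1 trial in 20, so the other 19 are analysed unadjusted. A p<0.20 trigger recovers somewhat more: on the level reading, about 81%, 82-83% and 86%.

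**Step 4: level against change.** In the same simulations the two unadjusted tests disagree on significance in about 27%, 22% and 20% of trials at r=0.3, 0.5 and 0.7.

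**Step 5: type I error.** With the p<0.05 trigger fixed in advance, it lies between about 3.6% and 5.0% over r and both readings. With p<0.20 on the level it is 4.6%, 3.7% and 2.7%. The test is conservative.

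**Step 6: the mixed-model wording.** I generated one data set with one week-24 value per patient and fitted both models. Ordinary regression gave a treatment estimate of −0.669 with residual variance 0.924. A model with a patient random intercept gave the same −0.669, split the variance arbitrarily in half (0.462 and 0.462) and warned that the Hessian was not positive definite. The random intercept is not identifiable, and the model reduces to linear regression.

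**The case against.** **The analysis is valid and meets its target.** On the level reading the conditional rule gives 81-82% at the design effect, against a planned 80%, and a fixed trigger does not inflate type I error. This stands, and it is why the point concerns efficiency and specification.

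**On the change reading, baseline HbA1c already enters by subtraction.** This also stands. At r=0.7 the loss is then only about 2 points. It remains about 9 points at r=0.5 and about 16 at r=0.3.

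**Thresholds and covariate lists belong in a SAP.** This is fair for the missing threshold. But the article states a rule, adjustment on observed imbalance, and a SAP that always adjusted for baseline HbA1c would depart from it.

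**Analysts are blinded.** The design overview and the Blinding section say so. This limits any choice of covariates in the app's favour, but it does not fix the covariates.

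**The joint longitudinal model uses every baseline value.** It does, but as a secondary analysis.

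A reader might infer three stronger conclusions.

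- *False positives are inflated.* The article does not describe picking whichever analysis is significant. If someone did so between unadjusted level and ANCOVA, the error would be about 6.3-8.4% for r from 0.3 to 0.7. That is a worst case the text does not support, given analyst blinding.
- *The primary model cannot be fitted.* The article never names the random effect in the primary model and elsewhere says linear regression. The wording is loose, and the treatment estimate is unaffected.
- *The rule leaves the trial underpowered.* The 67% figure arises only on the change reading at r=0.3, with 1.11 taken as the SD at each visit. If about 1.12 is instead the SD of change, unadjusted change has the planned 80%, and ANCOVA has 93.6%, 90.0% and 86.2% at r=0.3, 0.5 and 0.7.

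**Conclusion.** The point holds, as something that should be fixed. The article makes adjustment of the primary analysis depend on imbalance seen after randomisation, makes no commitment to baseline HbA1c, and gives two definitions of the primary outcome that are different tests when unadjusted.

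The cost in power at 0.6 is about 2 to 16 points on either reading. On the level it grows with r; on the change score it shrinks as r grows. The direction does not depend on the assumptions, because ANCOVA is at least as precise as either unadjusted analysis apart from one degree of freedom. The size does: it rests on a back-solved SD, equal at both visits, an assumed r, an assumed trigger and complete data on 55 per arm. Multiple imputation and the HbA1c entry limit were not modelled.

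The mixed-model wording is a minor inconsistency.

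**What to change.** Replace the adjustment sentence in Data analysis with: *The primary analysis is a linear model (ANCOVA) of week-24 HbA1c on treatment with baseline HbA1c as a prespecified covariate, whatever the observed balance, fitted in each imputed data set.*

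State one primary outcome definition in the Abstract, the Data set table, the design overview and the sample size section. Either will do, because subtracting baseline from the outcome changes only the baseline coefficient and leaves the treatment estimate the same. Fix any further covariates before unblinding, and reserve the mixed model for the analysis of repeated visits.

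The cost is one sentence and some consistent wording. Baseline HbA1c is already scheduled for every patient, so no data collection or sample size change is needed.
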